#### Control group

Loratadine (Shanghai Xianlingbaoya Medicine Co., Ltd., Shanghai, China) will be prescribed for oral administration at a dosage of 10 mg/day in the morning. Each treatment cycle will be for four consecutive weeks.

#### Concomitant care and intervention

During the treatment and follow-up period, the subjects are advised to avoid antigens. The participants are prohibited from taking medications such as oral and intranasal antihistamines, intranasal steroids, intranasal decongestant, antibiotics or oral leukotriene receptor antagonists. Only for patients with severe symptoms are intranasal steroids allowed to be used. The type of medicine, dosage and usage will be recorded in the diary card for analysis. For the other complicated chronic diseases, the patients must continue taking their routine medication and other therapies. The research staff will record the names of those diseases and the names of medications and therapies in the case report.

#### Discontinuation of the intervention

The intervention is to be terminated in the cases of severe adverse events, withdrawal of participants by their own wish and unpermitted medication use.

### Outcome measures

It has been found that similar outcomes have been applied in the previous studies on PAR, such as the Total Nasal Symptom Score (TNSS), the Total Non-nasal Symptom Score (TNNSS) [19, 20], the Rhinoconjunctivitis Quality of Life Questionnaire (RQLQ) [21–23], the Nasal Provocation Test [24], IgE level, eosinophil count [25], and Visual Analog Scale (VAS) [26]. The TNSS, TNNSS, and RQLQ have been adopted especially in this study due to their wide application.

#### Primary outcome measure

The average change in the TNSS will be measured blindly by comparing the baseline score in each group with that at 6 months after treatment during the follow-up period. The TNSS is determined in terms of the severity of rhinorrhea, nasal itching, nasal obstruction, and sneezing.

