**Fig. 1 Fig1:**
[figure not shown]
Flowchart of the study design

**Table 1 Tab1:** Study design schedule

Period	Screening	Baseline	Treatment (W1–4)		Follow-up (W5 − M6)	
Time	W − 1	W0	W2	W4	M3	M6
Eligibility	X					
Demography and medical history	X					
Physical examination	X					
Informed consent	X					
TNSS	X	X	X	X	X	X
TNNSS	X	X	X	X	X	X
RQLQ	X	X	X	X	X	X
Adverse event			X	X		
Compliance			X	X	X	X

*RQLQ* Rhinoconjunctivitis Quality of Life Questionnaire, *TNSS* Total Nasal Symptom Score, *TNNSS* Total Non-nasal Symptom Score

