#### Inclusion criteria

Participants will be eligible if they meet all of the following criteria: (1) are aged 18–60 years, (2) meet the classification criteria of moderate to severe PAR according to the Allergic Rhinitis and its Impact on Asthma (ARIA) guidelines, (3) exhibit at least one positive result on the allergy skin prick reaction test, (4) a 7-day mean Total Nasal Symptom Score (TNSS) ≥4 before treatment, and (5) agree to participate in the study willingly and voluntarily and sign the informed consent.

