### Study procedures

#### Recruitment

In order to achieve the target enrollments of participants, clinical recruitment flyers were placed in three hospitals. Clinical recruitment staff will be in charge of the enrollment process of the 98 participants with PAR. Participants will be screened based on the inclusive and exclusive criteria, be briefed on the purpose, procedures, treatments and possible risks of the trial, and be clearly inform of their rights to discontinue participation in the clinical study. The screening process takes about 1 week, requiring the participants to fill in questionnaires on symptoms during the 1-week period. Upon participants signing off the consent forms, the staff will then assign the recruited patients to different intervention groups.

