### Data collection and management

The research staff is responsible for the collection of baseline characteristic data and the allergen test results during the screening period. The baseline variables will include: center location, age, gender, highest education level achieved, employment, diagnosis, nasal mucosal examination result, allergen examination result, typical symptoms, occurrence time of symptoms, time of recurrence or aggravation, accessory examination of nasal mucosa and nasal sinus, family history, relevant diseases (allergic asthma, allergic conjunctivitis), other relevant clinical disorders (such as hypertension, diabetes, and cardiac arrhythmia), as well as the questionnaires such as the TNSS, the TNNSS, and the RQLQ.

Participants are required to record in the daily diary the symptoms of AR and intake of any other medications during this study period. Outcome evaluators will examine the outcomes at baseline, 2 weeks (within treatment), 4 weeks (end of treatment), 3 months (within follow-up), and 6 months (end of follow-up). Data on nasal symptoms, non-nasal symptoms, and patients’ quality of life will be collected.

Data monitoring and management will be performed by the Clinical Evaluation Center of CACMS every 3 months. Two assistants will enter all data into an electronic database by double data entry. The statistical manager will be responsible for source data organizing, coding, range checking for data values and converting data to ensure data quality.

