#### Statistical methods

The statistical analysis will be performed with SPSS 17.0 software (SPSS Inc., Chicago, IL, USA) in the Clinical Evaluation Center of CACMS. We will perform baseline adjusted analyses for the following variables (the center and severity), and the baseline value of the corresponding outcomes will be assessed. The data analyses will be conducted on an intention-to-treat population. Descriptive statistics will be used to compare the baseline measures and patients’ characteristics between the two groups. Regarding the primary and secondary outcome measures, the two-sample *t* test or Wilcoxon rank sum test will be used to compare the differences between the two groups from baseline to the end of treatment (*p* < .05 will be considered statistically significant). If an imbalance occurs in baseline characteristics between the two groups, ANCOVA will be applied.

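### The pre-treatment scores collected at W-1 and W0 are not built into the primary analysis: ANCOVA waits on an observed imbalance and the W-1 reading has no role, so precision is left unused

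*Protocol article*

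**What the plan says.** - **Schedule.** Table 1 ("Study design schedule") marks TNSS, TNNSS and RQLQ in both the screening column (W-1) and the baseline column (W0). Only W0 carries the baseline label.
- **Primary outcome measure.** The average TNSS change is obtained "by comparing the baseline score in each group with that at 6 months after treatment during the follow-up period". Secondary outcome measures treats the other TNSS time points and TNNSS in the same way. For RQLQ it names the assessment times but defines no change from baseline.
- **Screening data.** The entry rule is "a 7-day mean Total Nasal Symptom Score (TNSS) ≥4 before treatment". Recruitment describes a screening period of about one week, "requiring the participants to fill in questionnaires on symptoms during the 1-week period".
- **Evaluations.** Data collection and management lists one pre-treatment evaluation, at baseline, followed by those at 2 and 4 weeks and 3 and 6 months.
- **Analysis.** Under Statistical methods, "the two-sample *t* test or Wilcoxon rank sum test will be used to compare the differences between the two groups", and ANCOVA is applied if baseline characteristics turn out imbalanced. The section also announces baseline-adjusted analyses for center and severity, adding that "the baseline value of the corresponding outcomes will be assessed". It does not say that this value enters the primary model.
- **Separate plan.** Missing data and sensitivity analysis says that a full statistical analysis plan will be written. It is not shown.

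**The concern.** A nasal symptom score fluctuates from week to week. An unadjusted comparison of changes carries all the noise of the baseline measurement into every patient's outcome. Two standard remedies use data already in hand: adjust for the pre-treatment score in the model, and use more than one pre-treatment reading. As written, the first depends on observed imbalance and the second does not appear.

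What is at stake is the width of the interval for the month-6 TNSS difference in a trial of 98 patients, 39 per group after the expected dropout. Making the model depend on observed imbalance also leaves the form of the primary analysis open until the baseline data have been seen.

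**Working it through.** **The plan's own figure.** Sample size calculation gives mean TNSS changes of 4.90 (SD 3.54) and 3.4 (SD 1.0), 80% power, alpha 0.05 and delta 0.2.

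- Pooled SD = √[(3.54² + 1.0²)/2] = 2.601.
- Distance from the margin = (4.90 − 3.4) + 0.2 = 1.7.
- At one-sided 0.025: n = 2 × [2.601 × (1.960 + 0.842)/1.7]², rounded up to 37 per group (38 with the noncentral t). This is within 2 patients of the stated 39.
- The sidedness of alpha is not stated. One-sided 0.05 with the margin gives 29.
- Dropout: 39/0.8 = 48.75, so 49 per group and 98 in total, as stated.
- Power at 39 per group on these inputs is about 82%.

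**Effect of using the pre-treatment scores.** Scale the scores to unit variance at each time. Let b be the correlation between W-1 and W0, and r the correlation of either reading with month 6. The document gives neither; the assumed ranges are b = 0.6 to 0.8 and r = 0.3 to 0.5.

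- Change from one baseline: variance 2(1 − r).
- Change from the mean of two: 1 + (1 + b)/2 − 2r, a cut of (1 − b)/[4(1 − r)].
- ANCOVA on one baseline: 1 − r², a cut of (1 − r)/2 against the change score.
- ANCOVA on the mean of two: 1 − 2r²/(1 + b).

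| b | r | Change, one | Change, mean of two | Cut | ANCOVA, one | Cut vs change, one | ANCOVA, mean of two | Extra cut vs ANCOVA, one |
|---|---|---|---|---|---|---|---|---|
| 0.8 | 0.3 | 1.40 | 1.30 | 7.1% | 0.910 | 35% | 0.900 | 1.1% |
| 0.7 | 0.4 | 1.20 | 1.05 | 12.5% | 0.840 | 30% | 0.812 | 3.4% |
| 0.7 | 0.5 | 1.00 | 0.85 | 15.0% | 0.750 | 25% | 0.706 | 5.9% |
| 0.6 | 0.5 | 1.00 | 0.80 | 20.0% | 0.750 | 25% | 0.688 | 8.3% |

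The first and last rows give the ends of the quoted ranges for the second reading.

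**In power terms, on the planning inputs above.** A 12.5% cut (averaging two baselines in a change score, b = 0.7, r = 0.4) raises power at 39 per group from about 82% to 87%. A 25% cut (ANCOVA on one baseline, r = 0.5) raises it to about 91.5%, or lowers the required 37 per group to 28. These translations are indicative only, because the planning SDs describe change before and after treatment, not change to month 6.

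**Wider ranges.** With b from 0.5 to 0.9 and r from 0.2 to 0.6 (r not above b), the second reading saves 3.1% to 25% for a change score and 0.2% to 14.1% under ANCOVA. ANCOVA on one baseline saves 20% to 40% against the change score. The largest gain thus comes from the choice of model in most of this range.

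**The case against.** A reader might infer from the singular wording that baseline is one W0 reading and that W-1 serves for entry and is then thrown away. The document says neither. The wording fits W0, a weekly mean or a mean of both visits. The 7-day entry mean and the screening-week questionnaires make a multi-day TNSS baseline quite possible. W-1 and W0 could then be the two ends of one collection period, and a second TNSS reading would add almost nothing. This stands, and it limits the claim about the second reading. It does not touch the larger gain from adjustment, and the 7-day rule covers TNSS only.

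A reader might also infer a loss worth 8 to 25 patients out of 98 (98/0.929 ≈ 105.5 and 98/0.80 = 122.5). That holds only for an unadjusted change score under the assumed correlations. Nor can RQLQ be said to lose precision through change from one baseline score, since no RQLQ change from baseline is defined.

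Two technical objections have some force. The two readings may be obtained differently, and the entry cut truncates a pre-treatment score, so equal variances and equal correlations are approximations. This weakens the percentages but not validity: both readings precede treatment and are scheduled alike in both arms. Entering them as separate covariates does not require them to be exchangeable.

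Finally, deriving a baseline is usually a matter for the analysis plan, and the sentence on baseline-adjusted analyses may intend adjustment for the outcome's own baseline. The first part is fair, and an undefined baseline alone would not be a finding. But the article does fix a main test and a condition for ANCOVA, and that stated choice is less precise than one available from the same data.

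**Conclusion.** The point holds as an efficiency improvement. All three scales are scheduled at W-1 and W0, no described comparison uses the W-1 reading, and adjustment for the pre-treatment score is not the stated default.

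Under the assumed correlations, planned ANCOVA on one baseline cuts the change-score variance by about 25% to 35%. The second reading adds about 1% to 8% to that, or 7% to 20% if an unadjusted change score is kept, and possibly close to nothing for TNSS. All these figures rest on correlations absent from the document and on an equal-variance model. If the separate plan already prespecifies adjustment for the outcome's baseline, only the smaller gain remains.

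It would be going too far to conclude that the comparison is biased or the trial invalid. A randomized comparison of changes is valid without adjustment; it is merely less precise than it could be.

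**What to change.** - **Statistical methods:** make ANCOVA the primary analysis of month-6 TNSS whether or not imbalance is seen, with the W-1 and W0 readings, or their mean, as covariate. Do the same for TNNSS and RQLQ. Remove the imbalance condition.
- **Primary and Secondary outcome measures:** state which reading or readings form baseline for each scale and, for TNSS, how they relate to the 7-day mean. If W0 already summarizes the screening week, use that summary as the single covariate.
- **Entry rule:** leave unchanged.

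The cost is a few sentences here and in the separate analysis plan, settled before outcome data are examined. No new data, visit or patient is needed. A second covariate uses one degree of freedom.

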#### Secondary outcome measures

The average change in the TNSS will be measured by comparing the baseline score in each group with that at 2 and 4 weeks during treatment, 3 months after treatment during the follow-up period. The average change in the TNNSS will be reviewed blindly by comparing the baseline score in each group with that at 2 and 4 weeks, and 3 and 6 months after treatment. The TNNSS is determined in terms of the supplementary symptoms such as post-nasal discharge, tearing, nasal or ocular itching, nasal or maxillary pain, and headache. The RQLQ will be used to observe the effect on patients’ quality of life; this will also be evaluated at 2 and 4 weeks, and 3 and 6 months after treatment.

All outcome readings will be scored on quantitative scales, and will be summarized as mean values and standard deviation.

#### Safety evaluation of warm needling therapy

Adverse events such as burns, skin rash, pain or other adverse reactions will be recorded in detail, including time of occurrence, duration of symptoms, severity, management measures, time of adverse reaction disappearance, and any apparent correlation to the administration of warm needling therapy and/or medication. Clinical physicians will decide whether to cease the treatment according to the severity of the adverse events.

The total study period and the evaluation time points, see Fig. 2.

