The results from our previous international, multicenter clinical study in collaboration with South Korea revealed that 4-week long, active acupuncture treatment was significantly better at reducing AR symptoms compared with sham acupuncture and non-active treatment [13]. Furthermore, AR symptoms continued to reduce in the subsequent 4-weeks of follow-up, indicating the residual effect of acupuncture. Previous studies have demonstrated that moxibustion has a regulative effect on immune system function [14, 15]. Consequently, we have optimized the intervention scheme to warm needling. There are two types of warm needling, the one we used consists of placing an ignited moxa stick on the handle of the needle after insertion. Our hypothesis is that warm needling will achieve equal or better long-term symptom relief of AR and reduce its recurrence.

In previous studies of immunotherapy and pharmacotherapy effects on AR, the placebo control group treatment provided over 50 % symptom relief [16]. In previous clinical studies of AR treated with acupuncture therapy, placebo acupuncture was widely adopted as the control group. In this study, however, we have selected western medicine as the positive control instead of placebo acupuncture. Oral antihistamines are usually the first-line medication for AR symptom relief. Loratadine, as a second-generation antihistamine agent, has a strong selective antagonistic effect on the peripheral histamine H1 receptors, providing long-lasting effect without sedating the central nervous system. Not only is loratadine used in relieving and preventing AR-associated symptoms such as rhinorrhea, itching, sneezing, nasal blockage, and ocular symptoms [17, 18], it is also widely used in the treatment of other allergic diseases. After a detailed evaluation of the desired and the adverse effects, we chose loratadine as the intervention for the control group.

We have designed a multicenter, randomized controlled trial (RCT) for patients with PAR, using oral loratadine as control. The purpose of this trial is to answer two questions: (1) is the effect obtained by warm needling equal to or better than that achieved by loratadine? and (2) is the treatment of warm needling safe for patients with PAR?

The study was registered on ClinicalTrials.gov (NCT02339714).

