#### Follow-up

Upon completion of the 4-week treatment period, there is a further 6-month follow-up period. The research staff will continue to follow the participants via telephone communication and short messaging service (SMS). The frequency of follow-up is monthly and we will keep a record of the assessment of symptoms and medication compliance or changes. In the event of participants discontinuing or deviating from intervention protocols, the study staff will record the reasons for this and their medications and then exclude the participants from the study, and the latest outcome data including symptoms and frequency of the attacks.

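### No adverse-event collection is scheduled after week 4, so events still open then, or first noticed later, may be missed or left without a resolution date

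*Protocol article*

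**What the plan says.** The Background sets two questions for the trial. The first is efficacy against loratadine; the second is "is the treatment of warm needling safe for patients with PAR".

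The section Safety evaluation of warm needling therapy gives burns, rash and pain as examples. For each event it wants onset, duration, severity, management, "time of adverse reaction disappearance, and any apparent correlation to the administration of warm needling therapy and/or medication". It states no date on which recording ends.

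Table 1 (Study design) has a row "Adverse event" with marks at W2 and W4 and empty cells at M3 and M6.

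The Follow-up section states: "Upon completion of the 4-week treatment period, there is a further 6-month follow-up period". On content it states: "The frequency of follow-up is monthly and we will keep a record of the assessment of symptoms and medication compliance or changes".

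The section Data collection and management describes the diary: "Participants are required to record in the daily diary the symptoms of AR and intake of any other medications during this study period". The data it lists for the evaluations, which include months 3 and 6, are nasal symptoms, non-nasal symptoms and quality of life.

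**The concern.** The safety section asks for information that the schedule has no fixed occasion to collect. A burn, skin lesion or pain that is present at the week 4 visit needs an end date, but after that visit no form, contact or diary entry described in the article asks about it. The same holds for an event that a patient first notices, or first connects with treatment, after week 4.

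What is at stake is the completeness of the answer to the second trial question. Some events may have no resolution date, and delayed events would be recorded only if a patient volunteers them or a staff member happens to ask. Volunteered reports depend on the person and the site, so such data are hard to tabulate or to compare between arms.

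**Working it through.** The plan gives no figure on this point to reproduce. The check compares the schedule with the text and then works out the share of time covered.

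**Step 1. The schedule.** Post-baseline marks in Table 1:

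| Row | W2 | W4 | M3 | M6 |
|---|---|---|---|---|
| TNSS | X | X | X | X |
| TNNSS | X | X | X | X |
| RQLQ | X | X | X | X |
| Adverse event | X | X | – | – |
| Compliance | X | X | X | X |

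Adverse events form the only repeated row that stops at week 4. The row directly below it keeps all four marks, so a table damaged in extraction is an unlikely explanation.

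**Step 2. Other routes after week 4.**
- Monthly telephone or SMS contacts (Follow-up): symptoms and medication. Adverse events are not named.
- Daily diary (Data collection and management): rhinitis symptoms and other medication. Adverse events are not named.
- Month 3 and month 6 evaluations (same section): nasal symptoms, non-nasal symptoms, quality of life. Adverse events are not named.
- General statement in the Abstract that side effects will be observed and recorded: no time window and no collection point.

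**Step 3. What the safety section needs.** Duration and time of disappearance are required for each event. For an event that resolves by week 4, the schedule can supply both. For an event open at week 4, or starting later, no scheduled occasion supplies either. Both treatments run to the end of week 4 (Treatment group; Control group), so an event arising at the last needling session or with the last tablets has little or no scheduled observation after onset.

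**Step 4. Share of time covered.** Taking 6 months as about 26 weeks:
- month 6 counted from the end of treatment, as the Follow-up section has it: 4 / (4 + 26) = 0.133, about 13%;
- month 6 counted from baseline: 4 / 26 = 0.154, about 15%.

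So 85% to 87% of time on study has contacts and evaluations but no scheduled adverse-event item. This is a share of calendar time, not of expected events. The covered part is the whole exposure period, when most events tied to administration would be expected.

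**The case against.** The strongest reply is that nothing here is contradictory. A visit grid shows planned assessments and does not forbid completing an open record. The safety section sets no end date and asks for time of disappearance, which read plainly implies following an open event until it ends. The schedule covers the whole period of exposure in both arms. The reporting window and the content of contact forms often sit in the full protocol or case report form, and Publications and dissemination confirms that a fuller protocol exists.

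Much of this stands. It rules out saying that late events are lost: they may still be recorded if someone reports them. It does not remove the point, because the article prints a schedule that stops this one row at week 4 and describes three follow-up routes without naming adverse events. That is a stated schedule, not a detail left out. Fig. 2, which the safety section cites for the evaluation time points, was not available for this check. If it shows later adverse-event collection, it disagrees with Table 1 and the two still need reconciling.

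Three stronger readings are tempting and not supported:
- *That safety rests on two visits.* Patients are monitored by research assistants during the needling procedure (Precautions, under Treatment group), over 12 sessions, and control patients receive medicine weekly (Monitoring).
- *That the gap makes warm needling look safer than it is.* The schedule is the same in both arms. The session monitoring during treatment is described for needling only, so ascertainment may if anything be closer in that arm. No direction of bias can be derived.
- *That the compliance marks at months 3 and 6 are misplaced because treatment has ended.* The medication restrictions in Concomitant care and intervention continue through follow-up, so compliance has a meaning there.

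**Conclusion.** The point holds in a limited form. After week 4 no adverse-event collection is scheduled in either arm, although safety is one of two trial questions and each event is to have a duration and an end date. Events open at week 4, or first noticed later, may be missed or left without a resolution date. On-treatment collection is not in question.

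The gap covers about 26 of 30 weeks, or 22 of 26 if month 6 is counted from baseline. How many events fall in it cannot be estimated, because the documents give no rate of late or persisting events. The conclusion assumes that Table 1 is reproduced correctly and that the contacts and diary contain what the article says they contain. The primary outcome, sample size and efficacy analysis are unaffected. The change is worth making because it is cheap and bears directly on a stated objective.

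**What to change.** Reconcile Table 1 with the sections Follow-up and Safety evaluation of warm needling therapy:
- mark adverse events at M3 and M6 in Table 1;
- add one adverse-event question, worded identically in both arms, to each existing monthly contact;
- state that events open at week 4 are recorded until resolution or month 6, whichever comes first;
- report on-treatment and follow-up events separately by arm, so that later background events do not blur the comparison during exposure.

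No extra visits or patients are needed. With 98 participants and six monthly contacts each, the addition is at most 98 × 6 = 588 short answers, plus an item at the two evaluations where these are separate from the contacts. The downsides are slightly more data entry and some unrelated background events recorded during follow-up.
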